### Randomization

An unpredictable randomized sequence protocol was designed to allocate women in a 1:1 ratio to either the comparison (existing services) or intervention (NFP plus existing services) groups, and to ensure adequate concealment of randomization assignment [52]. A separate randomization schedule was generated for each of the 26 participating Local Health Areas within the Health Authorities using constrained randomization (permuted block design), wherein the smaller of the two block sizes is applied in areas where fewer than 18 women a year are expected to be randomized. The specific block sizes were chosen as the best trade-off between the loss of power associated with the use of block randomization and ensuring a balance in the number of women allocated to each trial group in the smaller sites, while also enabling management of NFP nursing workloads in both small and large Local Health Areas. The Scientific Team follows strict protocols for safeguarding administration of the group assignment schedule – to promote the integrity of allocation and to reduce the possibility of releasing assignments before a person has been verified as ready for that assignment [53]. Participants are counted as randomized as soon as the intervention allocation is issued and continue to be counted according to the group assigned, regardless of the course of intervention, according to intention-to-treat principles [53]. Participants are encouraged not to reveal their group allocation to the scientific field interviewers as the trial proceeds.

### Outcome indicators and measures

The BCHCP trial outcome indicators and measures were explicitly chosen to enable replication of some of the more robust US trial findings, while also addressing potential explanatory factors and indicators of salience for BC policy and practice. Tables 4 and 5 provide an overview of the measures at each assessment point. Names of validated scales/instruments are provided with citations, including those from which individual items were selected for this trial.

**Table 4 Tab4:** Maternal outcome indicators and assessment points

Outcome indicators (Measures^1^)	Baseline	34 weeks	Birth event	Two months	10 months	18 months	24 months
*Demographics and socioeconomic status*							
Age, racial/cultural group, language [63]	x	x		x	x	x	x
Education + employment [63]	x	x		x	x	x	x
Income + financial supports (Family Resource Scale Revised- Basic Needs) [63, 64]	x	x		x	x	x	x
Housing/residential stability [63]	x	x		x	x	x	x
Relationship status + demographics [11]	x	x		x	x	x	x
*Maternal health and functioning*							
Obstetric history [11]	x	x	x				
History of abuse or neglect (Childhood Trauma Questionnaire; Childhood Experiences of Violence Questionnaire) [65, 66]	x						
General health + long-term illness [67, 68]	x						x
Self-efficacy (Generalized Self-Efficacy Scale; Pearlin Mastery Scale) [69, 70]	x	x		x	x	x	x
Psychological wellbeing (Mental Health Inventory) [71]	x						
Anxiety + depression (Kessler Psychological Distress Scale) [72]	x	x		x	x	x	x
Prenatal nicotine + alcohol use^2^ [73, 74]	x	x					
Prenatal drug use [73]	x	x					
Intimate-partner violence (Composite Abuse Scale) [75]	x	x		x	x	x	x
Executive functioning (Stroop Colour-Word Task; Trail Making Test) [76, 77]	x						
Cognitive ability (Shipley-II) [78]	x						
Substance misuse [11]				x	x	x	x
Antisocial behaviour [79, 80]	x	x		x	x	x	x
Contraceptive use [11]				x	x	x	x
Subsequent pregnancies^2^ [11]				x	x	x	x

^1^Name of validated measure (items partially sourced from other measures indicated by citation)

^2^Secondary outcome indicators

**Table 5 Tab5:** Parenting and child outcome indicators and assessment points

Outcome indicators (Measures^1^)	Baseline	34 weeks pre	Birth event	Two months	10 months	18 months	24 months
*Parenting behaviours and beliefs*							
Breastfeeding initiation + duration [11]				x	x	x	
Provision of safe + nurturing home environment [11]				x	x	x	x
Parenting attitudes/beliefs (Adolescent-Adult Parenting Inventory II) [81, 82]						x	
Child exposure to 2nd hand smoke [83]				x	x	x	x
*Neonatal health*							
Pre-term birth			x				
Birth weight			x				
Apgar scores (1 + 5 min)			x				
Intensive care admission(s)			x				
*Child health and development*							
General health + long-term illness [67, 73]							x
Immunizations				x	x	x	x
Language (Ages and Stages) [84]					x	x	
Language + cognition^2^ (Bayley SID-III; MacArthur-Bates Communication Development Inventories) [85, 86]							x
Behaviour^2^ (Child Behavior Checklist) [87, 88]							x
Healthcare encounters for injuries^3^				x	x	x	x
Substantiated abuse or neglect				x	x	x	x
*Maternal and child service access and use*							
Prenatal programs	x	x					
Primary + secondary healthcare	x	x		x	x	x	x
Specialist care, e.g., mental health	x	x		x	x	x	x
Financial/educational assistance	x	x		x	x	x	x
Other services, e.g., housing	x	x		x	x	x	x
Parenting programs	x	x		x	x	x	x
Early child development programs				x	x	x	x
Other services	x	x		x	x	x	x
Barriers to essential services	x	x		x	x	x	x

^1^Name of validated measure (items partially sourced from other measures indicated by citation)

^2^Secondary outcome indicators

^3^Primary outcome indicator

#### Primary outcome indicator

The primary outcome indicator is child injuries from birth through 24 months. Independent data on healthcare encounters for child injuries will be obtained from personal records made available through secure data-sharing agreements with the BC Ministry of Health, which accesses and holds data on healthcare encounters across the province. These data sources include: BC Medical Services Plan physician billing records, which capture outpatient/community and emergency encounters (including dates of service and diagnoses); National Ambulatory Care Reporting System records, which capture emergency encounters (including dates of service, presenting complaints, discharge diagnoses and discharge dates); and Discharge Abstract Database records, which capture hospital encounters (including diagnoses and admission and discharge dates). These databases use diagnostic codes from the World Health Organization’s International Classification of Diseases (ICD) (9th and 10th editions). The trial will use the injury diagnosis codes and cause of injury codes pertaining to external injuries (e.g., fracture, burn, ingestion, open wound).

#### Secondary outcome indicators

The secondary outcome indicators are: prenatal nicotine and alcohol use; child cognitive development (language and cognitive ability) at age two years; child behaviour (internalizing and externalizing problems) at age two years; and the incidence of subsequent pregnancies by 24 months postpartum. (See Tables 4 and 5.)

### Frequency and nature of data collection to assess trial outcomes

Data are being collected via multiple methods and from multiple sources including: maternal self-report surveys, maternal and child observational and cognitive testing, and data linkage as well as data extracts. Scientific field interviewers verbally administer survey items and record the responses, to ensure comprehension and accuracy. For maternal self-report items prone to response bias, e.g., prenatal substance use and IPV exposure, questions are being administered using audiotaped recordings, with participants responding confidentially on paper and responses being placed in sealed envelopes. Data-sharing agreements were established between the Children’s Health Policy Centre at SFU and the BC Ministries of Health and Children and Family Development to facilitate data linkage regarding personal data (e.g., healthcare encounters for child injuries, substantiated cases of child maltreatment) documented in provincial datasets as well as NFP nurse assessment data. Data on neonatal outcomes are being provided through the BC Perinatal Database Registry.

Women participate in six data collection interviews from early in pregnancy until their child reaches two years of age. The interviews are conducted by scientific field interviewers: in person at baseline; by telephone at 34 weeks gestation; in person or by telephone at two months (to strengthen rapport and further encourage retention); in person or by telephone at 10 and 18 months postpartum; and in person at 24 months postpartum. Interviews typically take between 60 min (telephone) and 120 min (in person). Figure 1 depicts the participant pathways and interview schedule.

**Fig. 1 Fig1:**
[figure not shown]
Participant pathways and interview schedule

Scientific field interviewers have baccalaureate or master’s degrees, but no clinical training (in contrast with other recent NFP RCTs) [24, 25]. The Scientific Team therefore provides rigorous training that prepares interviewers to: rigorously assess socioeconomic eligibility criteria; manage large participant caseloads spanning wide geographic areas; track participants who have limited phone access and who move frequently; conduct in-depth interviews and record sensitive personal data in challenging community settings; follow intention-to treat protocols; build and sustain participant engagement with the trial; and discern and report adverse events.

Both prior to and during the trial, the Scientific Team at SFU provides research orientation sessions to NFP PHNs, supervisors, the BC Ministry of Health Provincial NFP Coordinator, and relevant Health Authority public health staff (e.g., managers, directors and administrative support staff) on “best-practice” procedures for RCT implementation.

### Participant retention

Based on a review of the research literature, the Scientific Team at SFU developed a detailed retention protocol [54–56]. This protocol includes the following steps and elements.Trial identification materials were developed including trial logo, business cards, letterhead and website;Participants are assigned to the same scientific field interviewer for the duration of the trial, wherever possible, to maintain strong trial rapport;Interviews are held at a wide range of times including on weekends to accommodate participants’ schedules;Participants receive gift cards after each interview to acknowledge their time and effort;Participants may contact the Scientific Team using a toll-free line, e.g., if they are moving or need to change appointments;Participants are contacted by their scientific field interviewer shortly before, and between, interviews using preferred modes of communication, e.g., texting;Participants receive birthday cards for their infants; andParticipants provide contact information for third parties (e.g., friends or family members) who scientific field interviewers may contact if they have difficulty reaching the participant.

A detailed tracking database captures participants’ progress through the trial, following Consolidated Standards of Reporting Trials (CONSORT) guidelines [57]. Informed consent is also being obtained to contact participants for long-term follow up – to set the stage for evaluating NFP’s impact across early childhood and beyond, including economic evaluation. The trial was also designed to not reveal the purpose to participants, but rather, to encourage them to share their experiences as young pregnant women and new mothers living in BC.

### Statistical analysis

A statistical analysis plan was developed for this RCT, providing a detailed summary of the data analysis methodology to be used. The trial statistician and Scientific Team will verify and approve the statistical analysis plan prior to any data being examined, to prevent biasing the analyses.

#### Sample size calculation

The sample size is based on a minimal clinically meaningful difference in the reduction of the number of physician encounters for injuries per child in community/outpatient, emergency and hospital settings – the RCT’s primary outcome indicator. In the BCHCP trial population, the base rate of injuries per child from birth through two years is expected to be 0.30 (30 %), based on aggregate-level BC data from a 10-year cohort of children born to first-time mothers receiving income assistance, provided by the BC Ministry of Health for the trial (unpublished report). This base rate is consistent with the rate of emergency room visits for injuries (accidents and ingestions) during children’s second year of life in a previous NFP trial in Elmira, US [14]. By consensus, the Scientific Team set the minimal clinically-meaningful reduction in risk as a relative risk of 0.70, i.e., a reduction from 0.30 (30 %) in the comparison group to 0.21 (21 %) in the intervention (NFP) group. With the probability of a type I error rate (alpha) set at 0.05 (2-tailed), a sample size of n = 495 per group is needed to detect a 30 % relative risk reduction with type II error (beta) set at 0.20 (power = 80 %). Presuming 5 % attrition only for the primary outcome indicator, due to accessing personal data from provincial datasets to measure this indicator, the estimated total sample size is 1040.

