## Methods/design

### Research aim

The aim of the trial is to evaluate NFP’s effectiveness compared with existing services in improving children’s mental health and early development and mother’s life circumstances. One primary outcome indicator has been identified: the average number of physician encounters per child for (intentional and unintentional) injuries, measured in community/outpatient, emergency and hospital settings from birth through to age two years. Four secondary outcome indicators have also been identified: prenatal nicotine and alcohol use; child cognitive development (language and cognitive ability) at age two years; child behaviour (internalizing and externalizing problems) at age two years; and the incidence of subsequent pregnancies by 24 months postpartum. (See Tables 4 and 5.) Potential explanatory factors such as maternal mental health (including self-efficacy) are also being assessed, as is the program’s impact on exposure to intimate-partner violence (IPV), a novel addition through the Canadian NFP curriculum [46]. Data are also being collected on health and social service access and use – to set the stage for long-term economic evaluation.

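### 495 per group gives 80% power only for Poisson means of 0.30 and 0.21 with variance equal to the mean; the percentage and risk wording does not match it, and extra variation in encounters would lower power

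*Protocol article*

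**What the plan says.** All references are to the protocol article.

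- *Research aim* defines the primary outcome as "the average number of physician encounters per child for (intentional and unintentional) injuries", over outpatient, emergency and hospital care up to age two. This is a mean count.
- *Sample size calculation* opens on the same unit, the "reduction of the number of physician encounters for injuries per child in community/outpatient, emergency and hospital settings".
- The base rate then appears in another unit and also as a percentage: "the base rate of injuries per child from birth through two years is expected to be 0.30 (30" per cent). Its source is an unpublished aggregate report from the Ministry of Health.
- The effect is a relative risk of 0.70, described as "a reduction from 0.30 (30 %) in the comparison group to 0.21 (21 %) in the intervention (NFP) group".
- Error rates are "type I error rate (alpha) set at 0.05 (2-tailed") and "type II error (beta) set at 0.20 (power = 80" per cent). The result is "a sample size of n = 495 per group is needed to detect a 30 % relative risk reduction"; with 5% attrition the total is 1040.
- The base rate is called "consistent with the rate of emergency room visits for injuries (accidents and ingestions") in the second year of life in the Elmira trial.

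The section gives no variance, no dispersion factor and no ratio of encounters to injuries. *Statistical analysis* names Poisson and Normal multilevel models and leaves the equations to the SAP, which is not shown.

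**The concern.** One paragraph describes the same 0.30 in three ways: as the basis for an encounter endpoint, as a rate of injuries, and as a percentage with a risk reduction. These imply different variances, so they imply different sample sizes for the same power.

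The choice matters for this endpoint. *Primary outcome indicator* draws on physician billing, emergency and hospital discharge records. One injury can therefore produce several encounters, and some children are injured repeatedly. Both tend to make the variance of a count exceed its mean.

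The stated power is what readers will use to judge a null result on the only primary outcome. If it rests on an unstated variance assumption that the endpoint may not meet, such a result could be taken as better evidence against a ratio of 0.70 than the design supports.

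**Working it through.** **Inputs** (*Sample size calculation*): rates 0.30 and 0.21, difference 0.09, two-sided alpha 0.05 (z = 1.96), power 80% (z = 0.8416). Allocation is 1:1 (*Randomization*). Total 1040 less 5% attrition leaves 1040 × 0.95 / 2 = 494 per arm.

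**1. Reproduce 495 as two Poisson means, variance equal to the mean.**

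n = (1.96 + 0.8416)² × (0.30 + 0.21) / 0.09² = 494.2, rounded up to 495. The match is exact. Variants on the log and square-root scales give 499.5 and 490.3.

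**2. Try 30% versus 21% as proportions of children.**

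With pooled p = 0.255:

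n = [1.96 × √(2 × 0.255 × 0.745) + 0.8416 × √(0.30 × 0.70 + 0.21 × 0.79)]² / 0.09² = 367.

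With continuity correction n = 389. Other standard formulas (unpooled, arcsine, log relative risk, log odds ratio) give 364 to 376. With 495 per group the power for these proportions would be 90%, not 80%.

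**3. Add variation beyond Poisson.**

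With mean encounter rate μ in the comparison group, rate ratio R and variance/mean φ:

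n = (1.96 + 0.8416)² × φ × (1 + R) / [μ × (1 − R)²].

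For μ = 0.30, R = 0.70 and 494 per arm, power = Φ(0.09 / √(0.51 × φ / 494) − 1.96). The φ values below are assumptions; the document gives none.

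| φ | Power at 494 per arm | n per arm for 80% |
|---|---|---|
| 1.0 | 80% | 495 |
| 1.25 | 71% | 618 |
| 1.5 | 63% | 742 |
| 2.0 | 51% | 989 |

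At φ = 1.5 and μ = 0.30, solving (1 − R)² / (1 + R) = 7.849 × 1.5 / (0.30 × 494) = 0.0794 gives R of about 0.64 as the ratio detectable with 80% power.

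**4. If 0.30 counts injuries and each injury yields M encounters.**

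For Poisson injuries the difference becomes 0.09 × E[M] and the summed variance 0.51 × E[M²]. The required n is therefore 494.2 × E[M²] / E[M]², that is, 494.2 × (1 + CV² of M).

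- Constant M: the factor is 1 and power stays at 80%. Simulation with exactly two encounters per injury at 495 per group gave 79.9%, although the encounter variance is then twice the encounter mean.
- Half of injuries with one encounter, half with two (assumed): 2.5 / 1.5² = 1.11, power 76%.
- One, two, three or four encounters in 60/25/10/5% of injuries (assumed): 3.3 / 1.6² = 1.29, power 69%.

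**5. The offset.**

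In the formula of step 3, n depends on φ/μ. With μ = 0.45 and φ = 1.5, φ/μ = 3.33, the same as 1.0 / 0.30, so power returns to 80%.

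**The case against.** The best defence is that endpoint, sample size and model family agree. The endpoint is a mean count per child, 495 is the Poisson answer, and Poisson models are named for analysis. Nowhere does the text say that the percentages are of children. On this view the percentage and risk terms are loose notation. Much of this stands. A reader might infer an arithmetic error in 495, and the document does not support that: the figure follows exactly from 0.30 and 0.21 as Poisson rates.

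The 0.30 may also already count encounters. The Ministry data that the article describes are billing, ambulatory and discharge records, and the section offers 0.30 as the base rate for an encounter endpoint. The report is unpublished, so this cannot be settled. If it is so, step 4 drops out and only ordinary overdispersion (step 3) remains.

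A reader might infer that 80% is a ceiling. That goes too far. It would need a true rate no higher than 0.30, no underdispersion (φ = 0.8 would give 88%) and no gain from covariate adjustment, which *Statistical analysis* allows for. Step 5 shows that a higher rate can restore the loss.

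The unseen SAP may allow for extra-Poisson variation. That would protect the standard errors, but it would not make good the power stated here.

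On Elmira, the section itself discloses that the comparison is with emergency visits in one year, and the comparison does not enter n. What remains is that a rate over two years and all settings is not corroborated by a rate of a different kind.

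**Conclusion.** The concern stands as a fault in what the sample size section states, not in its arithmetic. The percentage and risk wording does not match 495: as proportions the same figures need 367 to 389 per group with the pooled formula. The section moves between encounters and injuries without saying how they relate. Its 80% relies on an unstated condition, variance equal to the mean.

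If the base rate is 0.30 and encounter counts vary more than Poisson, because encounters per injury vary or children differ in risk, power for a ratio of 0.70 is below 80%. This assumes that the 30% reduction carries over to encounters and that covariates bring no gain.

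The direction is firm under those conditions; the size is not. A reader might take the 71%, 63% and 51% above as the trial's actual power. They are illustrations at assumed dispersion, and the document gives nothing to choose among them.

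**What to change.** Keep N and keep encounters as the unit; moving to injury episodes would change the primary endpoint.

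1. Restate 0.30 and 0.21 as mean encounters per child over 24 months, with a rate ratio of 0.70, and drop the percentage and risk wording.
2. Confirm from the Ministry's existing cohort report whether 0.30 counts encounters or injuries. Obtain the mean and variance of encounters per child in that cohort. If 0.30 proves to count injuries, use the encounter mean in item 1.
3. Restate power and the detectable rate ratio at that mean and dispersion, or give a table for variance/mean from 1.0 to 2.0. Do this before any outcome data are examined.
4. Describe the Elmira comparison as not like for like. This does not affect n.

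The cost is a wording change and one aggregate request to a partner that already supplied the base rate. The drawback is that the stated power is likely to become less favourable, unless the encounter rate proves high enough to offset the dispersion.

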#### Statistical analysis

The primary and secondary analyses will be conducted on an intention-to-treat basis. We will use the most recent version of MLwiN multilevel modeling software for the statistical analyses of our primary and secondary outcomes [58]. Equations for the multilevel regression models are stated in the statistical analysis plan for outcomes with Poisson and Normal distributions. Prior to analysis, data will be checked for outliers, inconsistencies and possible transformation. We predict that our sample size will be large enough for our statistical tests to be robust in the face of non-normally distributed variables. To reduce bias and loss of statistical power in our analysis of primary and secondary outcome indicators, we will use multiple imputation to estimate values for missing variables.

Descriptive statistics regarding baseline demographic, socioeconomic and personal risk variables will be used to identify any variables with a standardized difference between the groups of *d* > 0.05 for consideration as a candidate variable for control in the analyses. We do not expect differences among Local Health Areas in the implementation of NFP due to the rigorous education and manualized delivery of the program following core model elements. Nevertheless, we will use Local Health Area (site) for stratification purposes and test for between-site differences in NFP versus existing services outcomes.

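### Baseline variables are screened for adjustment by a between-group difference of d > 0.05, which is smaller than one standard error of chance imbalance and takes no account of prognostic value

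*Protocol article*

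**What the plan says.** The rule is in the last paragraph of the Protocol article's Statistical analysis subsection. The material screened is "Descriptive statistics regarding baseline demographic, socioeconomic and personal risk variables", and these statistics "will be used to identify any variables with a standardized difference between the groups of" d > 0.05. A flagged variable is put forward "for consideration as a candidate variable for control in the analyses". The article does not state how many variables are screened, how a candidate gets into the model, or whether its relation to the outcome counts. The same paragraph uses Local Health Area for stratification.

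The opening paragraph of the Statistical analysis section says that the trial statistician and Scientific Team "will verify and approve the statistical analysis plan prior to any data being examined, to prevent biasing the analyses". The model equations are left to the statistical analysis plan, which is not shown.

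**The concern.** Covariate adjustment in a randomized trial earns its place by explaining variation in the outcome. A screen on observed imbalance selects on something else. In a properly randomized trial, imbalance is chance, and a cut-off below one standard error flags mostly noise. A strong predictor that happens to be balanced is not flagged. The precision it could have given is then lost unless the variable enters the model by another route.

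The candidate list is also known only once baseline data have been compared by group, and the step from candidate to model is open. The covariate set therefore depends on the random draw and on a judgement made after that comparison. This undercuts the stated purpose of approving the plan before data are examined. At stake are some power for outcomes with a strong baseline predictor, a test that no longer has its nominal size, and a covariate set that cannot be known beforehand.

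**Working it through.** **Inputs.** Allocation is "to allocate women in a 1:1 ratio" (Randomization), and "the estimated total sample size is 1040" (Sample size calculation), so 520 per arm. The evaluable number comes from "a sample size of n = 495 per group is needed to detect" the target effect. Rates are 0.30 and 0.21, two-sided alpha 0.05, power 80%. Baseline-outcome correlations and the number of variables screened are not given, so they are assumed below and shown as ranges.

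**The plan's own figure.** Comparing two Poisson rates on the difference scale:

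n = (1.960 + 0.842)² × (0.30 + 0.21) / 0.09² = 494.2, so 495 per arm.

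990 × 1.05 = 1039.5, so 1040. The sample size is reproduced as an unadjusted rate comparison and is not in dispute.

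**The cut-off against chance.** Under randomization SE(d) ≈ √(2/n per arm). Stratification by Local Health Area is ignored here; it matters little for variables unrelated to site.

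| n per arm | SE(d) | 0.05 / SE | P(\|d\| > 0.05) |
|---|---|---|---|
| 520 | 0.0620 | 0.81 | 42% |
| 495 | 0.0636 | 0.79 | 43% |

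- If d is read as signed, the chance at 520 per arm is 21%.
- For 0.05 to equal one standard error, n = 2/0.05² = 800 per arm.
- If 10, 20 or 30 independent variables were screened (assumed), about 4, 8 or 13 would be flagged with nothing wrong.
- Any one predictor, however strong, goes unflagged with probability 1 − 0.42 = 0.58.

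**Power, Normal outcome.** Simulation with 520 per arm, 20,000 runs per setting and one covariate with assumed correlation ρ. The effect is set for 80% unadjusted power: 2.8016 × √(2/520) = 0.174 SD. The rule is applied mechanically: adjust if |d| > 0.05, otherwise do not.

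| Assumed ρ | Unadjusted | Always adjusted | d > 0.05 rule | Loss vs always adjusted (points) | Type I error under rule |
|---|---|---|---|---|---|
| 0 | 80.4% | 80.4% | 80.4% | 0.0 | 4.9% |
| 0.3 | 80.2% | 83.5% | 82.0% | 1.5 | 4.5% |
| 0.5 | 79.9% | 90.0% | 85.9% | 4.2 | 3.9% |
| 0.7 | 80.3% | 97.5% | 90.9% | 6.6 | 2.9% |

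Differences were taken before rounding. The always-adjusted column agrees with Φ(2.8016/√(1 − ρ²) − 1.96), which is 83.6%, 89.9% and 97.5% for ρ = 0.3, 0.5 and 0.7. Type I error falls because the unadjusted standard error is used exactly when the groups are balanced on the covariate, and it is then too wide.

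**Power, Poisson primary outcome.** Rates 0.30 and 0.21, 495 per arm, 1,500 runs, Monte Carlo error about 1 point.

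| Assumed log-rate coefficient per SD | Unadjusted | Always adjusted | d > 0.05 rule |
|---|---|---|---|
| 0.3 | 80.5% | 80.5% | 80.4% |
| 0.6 | 78.4% | 81.3% | 79.3% |

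The loss against always adjusting is about 0 to 2 points.

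**Where a strong predictor exists.** Table 4 shows prenatal nicotine and alcohol use measured at baseline and at 34 weeks. Tables 4 and 5 show no baseline value for child injuries, cognition and language, behaviour or subsequent pregnancies. The high-correlation rows therefore apply mainly to one of the four secondary indicators.

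**The case against.** Much of the case on the other side stands.

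- **No contradiction.** A reader might infer that the rule breaks the commitment to approve the plan before data are examined. It does not. A selection rule written into a plan beforehand is compatible with that sentence; only its aim is weakened.
- **Candidates only.** A reader might infer that flagged variables automatically enter the model, or that baseline nicotine use is adjusted for only when imbalanced. The text says neither. The unseen analysis plan may name further covariates or define the second step, and nothing says that outcomes inform the choice.
- **The comparator matters.** Against an unadjusted analysis the rule gains power where the covariate is prognostic. The sample size rests on an unadjusted comparison, so the planned 80% is not reduced by the rule.
- **No inflation when applied mechanically.** Type I error falls rather than rises.
- **Larger losses need assumptions that the documents do not supply.** At 500 per arm, an effect of 0.12 SD and a correlation of 0.7, one can obtain 75% against 58%. But 0.12/√(2/500) = 1.90 corresponds to only about 47% unadjusted power, well below the design's 80%, and neither input is in the article.
- **A low cut-off means adjusting more often.** Raising it would make matters worse: at 0.10 only about 11% of variables would be flagged by chance, so balanced predictors would be missed more often.

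The stated criterion remains a poor one. It selects on imbalance, at a level that cannot be told from noise, and does not mention prognosis. That is a statement in the article, not a detail left to another document.

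**Conclusion.** The point holds as a moderate one. The 42% chance-flagging figure follows from the article's own sample size. The power figures rest on assumed correlations, a single covariate and mechanical use of the rule. Compared with pre-specified adjustment, the loss is roughly 2, 4 and 7 points for a Normal outcome at correlations of 0.3, 0.5 and 0.7, with type I error down to about 3% at 0.7. There is no loss if the covariate is not prognostic. For the primary outcome the practical issue is less the 0 to 2 points of power than a covariate set that is not known until group-level baseline data have been seen.

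**What to change.** Drop d > 0.05 as a rule for selecting covariates. Before allocation is linked to any data, name in the analysis plan a short list of prognostic covariates to be used whatever the imbalance: the baseline value of the outcome where one is collected (nicotine and alcohol use), maternal age, and one socioeconomic indicator. Keep Local Health Area as already planned. Report standardized differences for description, or use them to define a sensitivity analysis labelled as such. If the analysis plan already contains such a list, it is enough to say that the list governs and that the screen does not change the main models.

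The cost is a change of wording. Table 4 shows that these variables are already collected at baseline, and neither the sample size nor the visit schedule is affected.
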